### Sample size

An *a priori* power analysis (α = 0.05, power = 80%) was performed for the primary measure of interest: fall risk based on Mini-Balance Evaluation Systems Test (Mini-BESTest) scores. A study by Conradsson, et al. that measured fall risk with the Mini-BESTest following a fall prevention intervention, found a 3-point change in Mini-BESTest scores in the intervention group and a large effect size (Cohen’s d = 0.82) (Conradsson et al., 2015). In addition, Godi et al. performed a reliability, validity, and responsiveness study of the Mini-BESTest and determined the minimal detectable change (MDC) at the 95% confidence interval was 3.5 points (Godi et al., 2013). Based on these previous findings, the power analysis indicated *at least 22 participants per group are needed*. To account for 30% participant attrition, 30 participants per group will be targeted (3 groups, total of 90 participants).

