#### Intervention

There are two interventions and one control activity being compared in this study: prescribed use of minimal footwear, IFM strengthening exercises, and a sham intervention of seated active range of motion of the upper and lower extremities with no foot muscle involvement, accompanied by a brochure with home fall prevention recommendations (control activity). All intervention activities will be prescribed 5 days per week for 16 weeks. After the 16-week intervention period, participants will be encouraged to continue their intervention at least 2 days per week until the end of the 12-month study to maintain gains in muscle strength or endurance (American College of Sports Medicine et al., 2018). At least 2 days of continued training is recommended by the American College of Sports Medicine to maintain muscle strength and endurance (American College of Sports Medicine et al., 2018).

Those in the minimal footwear group will be given a standardized pair of minimal shoes (Figure 3. Xero Aptos, Xero Shoes, Broomfield, CO, United States), and detailed instructions regarding gradual progressive use of the minimal footwear (Supplementary Material). In brief, the instructions include 30 min per day of continuous or non-continuous walking at a self-selected pace (using an assistive device as needed), and also wearing the footwear for progressively longer periods during daily activities.

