#### Statistical analysis

Fall risk (MiniBESTest scores), muscle CSA of five IFM, Lower Extremity Position Test scores, navicular drop, and hallux valgus angle data will be compared using a *three-group x four-time points* repeated measures analysis of covariance (ANCOVA).

Fall rate will be measured using the number of falls per person in a 12-month period, beginning with the date of the baseline measure. A Cox proportional hazards model will be used to compare falls across groups.

Demographic and potential confounding variables will be collected and included in analyses (e.g., age, sex, height, weight, race, ethnicity, education, pre-trial physical activity (quantified based on the Physical Activity Guidelines for Americans, older adults) (Piercy et al., 2018), pre-trial falls history, comorbidities, medications, self-reported visual impairment, and grip strength).

Implementation variables will be analyzed quantitatively via adherence records and Likert scales, as well as qualitatively via semi-structured interviews.

Our primary analytic approach is an intention to treat analysis. We also will conduct a per protocol analysis for participants who do not complete all study activities (missing data). This may include analysis for mechanisms of missingness: missing completely at random (MCAR), missing at random (MAR) or missing not at random (MNAR). Based on the mechanism of missingness, we may perform a listwise or case deletion or last observation carried forward if appropriate. (Kang, 2013).

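### The only missing-data methods named are case deletion and LOCF, to be chosen by a mechanism the data cannot identify, and the per-protocol set is worded in reverse

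*Protocol article*

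**What the plan says.** All of the following is from the protocol article.

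- **Statistical analysis, primary approach:** "Our primary analytic approach is an intention to treat analysis".
- **Next sentence:** "We also will conduct a per protocol analysis for participants who do not complete all study activities (missing data", where the parenthesis equates non-completion with missing data.
- **Then:** the missingness may be classified as completely at random (MCAR), MAR or MNAR, and "Based on the mechanism of missingness, we may perform a listwise or case deletion or last observation carried forward if appropriate".
- **Main model (same section):** a repeated measures ANCOVA with three groups and four time points (baseline, 8 weeks, 16 weeks, 12 months).
- **Sample size:** "at least 22 participants per group are needed", and "To account for 30% participant attrition, 30 participants per group will be targeted (3 groups, total of 90 participants".
- **Intervention:** activities are prescribed 5 days per week for 16 weeks. After that, "participants will be encouraged to continue their intervention at least 2 days per week until the end of the 12-month study".
- **Anticipated results:** cold weather may limit footwear use and foot stiffness may hinder the exercises. No limitation is expected in the control group.

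No other section names a further missing-data method or restates the per-protocol set.

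**The concern.** There are three linked problems.

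1. **The selection rule cannot be carried out.** MCAR can be partly checked against observed data. MAR and MNAR cannot be told apart from observed data, and that is the distinction on which a valid analysis turns. Because the wording is also permissive, the method would be settled after the data are seen.
2. **The two named methods suit this trial poorly.** Deletion discards randomised participants, which conflicts with intention to treat. LOCF keeps them but fixes their score at the last visit. For someone last seen at week 16, that assumes full maintenance across the step-down from 5 to at least 2 days per week, which is what the 12-month visit is there to measure.
3. **The per-protocol set is inverted.** Read literally, it consists of people who did not complete. It also treats stopping the activity and missing a measurement as one event. A participant can stop exercising yet attend every visit, or adhere fully and miss one.

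At stake are the size and possibly the sign of the bias in the Mini-BESTest comparison, the number of participants behind it, and whether a supportive analysis describes the people its name implies.

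**Working it through.** **Step 1. The plan's own figures.** Inputs from Sample size: alpha 0.05, power 80%, d = 0.82. Sidedness is not stated, so two-sided is assumed. For a comparison of two groups by normal approximation:

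n = 2(1.960 + 0.842)² / 0.82² = 23.4, so 24 per group.

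This is within 2 of the stated 22. A one-way three-group ANOVA with an assumed f of 0.40 gives 21.1, which rounds up to 22. The stated figure is therefore reproducible and is not in dispute.

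**Step 2. What deletion costs.** 30 × (1 − 0.30) = 21 per group, and 3 × 21 = 63 of 90. This is the most that deletion would leave at that attrition, because a single missed visit also removes a participant from a complete-row analysis. Pairwise power = Φ(0.82 × √(n/2) − 1.960):

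- n = 21: Φ(2.657 − 1.960) = 75.7%
- n = 22: Φ(2.720 − 1.960) = 77.6%
- n = 30: Φ(3.176 − 1.960) = 88.8%

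The last figure is an upper bound. A likelihood or imputation analysis of all 30 recovers only part of the lost information.

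**Step 3. Direction of LOCF bias.** In one arm, bias = p × (mean gain of leavers at their last visit − their mean gain at 12 months), where p is the share who leave. If they leave while gains are still building, the bracket is negative and LOCF understates the gain. If they leave at the peak and gains then fade, it is positive and LOCF overstates it. The protocol fixes neither the timing of dropout nor the course of the gains.

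**Step 4. Illustration.** None of these inputs is in the protocol except the 3 points and d = 0.82.

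- SD = 3/0.82 = 3.66; correlation between visits 0.7.
- Active gain 1.5 points at week 8 and 3.0 at week 16 and 12 months; no change in control.
- All dropout comes after week 8. Under MAR, a smaller week-8 change makes leaving more likely.
- 300,000 simulated participants per arm; true 12-month difference 3.0.
- The MAR-based estimate predicts missing 12-month scores within arm from baseline and week 8.

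| Mechanism | Dropout active/control | LOCF | Deletion | MAR-based |
|---|---|---|---|---|
| MCAR | 30%/30% | 2.56 | 3.01 | 3.01 |
| MCAR | 40%/20% | 2.39 | 2.99 | 2.99 |
| MCAR | 20%/40% | 2.70 | 2.99 | 2.99 |
| MAR | 30%/30% | 2.56 | 3.02 | 3.02 |
| MAR | 40%/20% | 2.30 | 3.30 | 3.01 |
| MAR | 20%/40% | 2.82 | 2.73 | 3.01 |

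Step 3 agrees with the first row: 0.30 × (1.5 − 3.0) = −0.45, so 2.55. In this setting LOCF is biased in all six rows, even under MCAR. Deletion is biased when dropout is MAR and unequal by arm, in a direction set by which arm loses more people. Unequal dropout is plausible here because the protocol foresees adherence barriers only in the active arms.

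**Step 5. The per-protocol wording.** A per-protocol set normally holds those who followed the assigned activity. The sentence names those who did not complete, and its parenthesis makes this a matter of missing data. The journals described under Intervention and under Qualitative and implementation data record adherence separately from attendance, so the two can be kept apart.

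**The case against.** **Readings that go too far.**

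- A reader might infer that both methods favour the active arms. The documents do not support this. In the illustration LOCF ran against the active arms in every row, and deletion went either way.
- A reader might take a 3-point gain at week 16, let 30% leave afterwards with a true 12-month gain of 1.5 or 0, and find LOCF too high by 0.30 × 1.5 = 0.45 or 0.30 × 3 = 0.90 points, which is 22.5% to 45% of the 2-point MCID. If only the leavers fade, unobserved, that is MNAR. A mixed model or multiple imputation under MAR would be wrong by about the same amount. The figures therefore argue for an MNAR sensitivity analysis, not for changing the primary method. The protocol also does not say that the 30% falls after week 16, and 12 months is not named as the primary time point.
- A reader might infer that intention to treat is nullified. The methods are conditional, and the per-protocol analysis is an addition that leaves the intention-to-treat set as it is.

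**What else can be said for the plan.**

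- The deletion/LOCF sentence follows the per-protocol sentence and may belong only to it. The primary analysis would then have no stated missing-data method, which an article may leave to a fuller document. This reading is fair, but the text does not settle it, and a classical repeated measures ANCOVA needs complete rows, so deletion remains a real possibility. The named methods and the reversed set are unsuitable on either reading.
- MCAR can be partly checked, deletion is unbiased under MCAR, and the two-weekly contacts gather relevant information. This stands: the rule is incomplete rather than empty. It still fails at MAR versus MNAR.
- The fall to 21 per group is largely built into the design, since 22/0.70 = 31.4, or 32, would have been needed to keep 22. This also stands: the shortfall is one participant per group and is not new harm.
- The per-protocol sentence may be loose wording for an analysis that accounts for non-completers. That is possible, but the protocol does not say so.

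**Conclusion.** The point holds and should be fixed, though it does not invalidate the design. The protocol states specific methods here rather than leaving them open, so this is not a matter of detail reserved for an analysis plan.

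What rests on the text alone is that only deletion and LOCF are named, that the choice depends on a distinction the data cannot make, that deletion conflicts with intention to treat, and that the per-protocol set is reversed. What rests on the plan's own figures is 63 of 90 analysed under deletion, with pairwise power near 76% at d = 0.82 (two-sided, normal approximation). The sizes of bias, 2.30 to 2.82 for LOCF and 2.73 to 3.30 for deletion against a true 3.0, depend on the assumed dropout timing, gains and correlation. They show that bias of several tenths of a point can arise; they do not predict its direction in this trial.

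**What to change.** 1. **Primary intention-to-treat analysis.** Remove deletion and LOCF. Pre-specify one likelihood-based mixed model for repeated measures, or multiple imputation by arm, that uses all randomised participants and is valid under MAR. Allocation is stratified on the baseline Mini-BESTest, so every randomised participant has that score. Treating baseline as one of the four time points keeps people with no later visit in the model.
2. **Sensitivity analysis.** Add a delta-adjusted or reference-based analysis for MNAR. This is what addresses gains that fade unseen after dropout. Drop the step that selects a method by classifying the mechanism.
3. **Per-protocol set.** Redefine it as participants who meet an adherence threshold, set in advance and taken from the journals. Keep it separate from missing outcomes and label it supportive only.
4. **Scope.** State which analysis each missing-data method serves.

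The cost is revised analysis wording and modest programming. No extra participants, visits or measurements are needed. The change should be made before outcome data are analysed.

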### Anticipated results

We hypothesize that both IFM strengthening exercises and prescribed minimal footwear use will result in reduced fall risk exceeding the established MDC (3.5 points) or MCID (2 points), improved proprioception, and increased IFM size (CSA), and will result in no change in foot structure measures. Those participants performing IFM strengthening exercises will likely have greater changes in muscle size than those using minimal footwear due to the intentional recruitment of the IFM. However, the changes in fall risk and proprioception will likely not differ significantly between minimal footwear use and IFM strengthening exercise groups. We hypothesize no changes will occur with fall risk, proprioception, IFM size, and foot structure in the control group.

It is unknown how our cohort of older adults will receive the IFM strengthening exercises or minimal footwear, but based on limited evidence in nations outside the United States, some older adults can successfully perform these interventions. Our study will be conducted in a region with cold weather, which could limit adherence to minimal footwear use. We plan to encourage participants to use footwear in large indoor spaces such as shopping malls. Severe foot and toe stiffness could make performance of the IFM strengthening exercises difficult for some individuals. We do not anticipate any limitations for the control (sham intervention) group.

Several factors have been included in the study design in an effort to keep participants engaged in the study for 12 months. We have seven in-person meetings planned for measurement and intervention instruction and review. In addition, each participant will have two specific Doctor of Physical Therapy students assigned to them for intervention instruction, intervention review, scheduling, and bi-monthly contacts. This personal connection may keep participants adherent and engaged in study activities.

## Discussion

Strengthening of the IFM in older adults may lead to a reduction of falls and injuries in this population, but this is not yet established. The aims for this study address multiple gaps in the literature. First, this study can improve our knowledge of the IFMs’ role in balance and mobility in older adults. Second, this study seeks to establish an effective approach to improving IFM strength in older adults. Evidence is limited regarding the best interventions by which to strengthen and/or enhance proprioceptive abilities of foot structures, specifically the IFM (Futre et al., 2022). The function of the IFM in terms of proprioceptive or motor control qualities is largely speculative and has not been objectively measured in older adults (Futre et al., 2022). A recent systematic review of IFM-related studies (Jaffri et al., 2023) found only two studies that objectively measured effects on sensory or motor control function. One study found improvements in proprioception and balance following IFM strengthening; however, participants in this study were 19–29 years old (Lee et al., 2019). The other found improved motor performance with IFM exercises after a 4-week intervention, with a mean age of participants of 21.5 years (Fraser and Hertel, 2019a). To date, there are no known investigations regarding proprioceptive, sensory, or motor control effects of IFM strengthening interventions in older adults. Subjectively, older adults who have performed IFM strengthening interventions report improved foot and/or lower extremity awareness and improved balance (Futre et al., 2022). This suggests an important somatosensory contribution of the IFM that is largely unexplored in older adults. Finally, isolated IFM strengthening interventions may have an impact beyond the foot. The local changes in foot strength and/or proprioception may lead to improved balance and functional mobility, reduced falls, and promotion of greater physical activity in older adults (Futre et al., 2022).

Physical therapists and other healthcare providers could incorporate IFM strengthening interventions into rehabilitation, fall prevention, and physical activity programs, potentially by wearing minimally cushioned footwear during exercise or daily activities, or by teaching older adults how to safely perform and integrate specific IFM strengthening exercises into their routine. These interventions could be conducted at a community-wide level at senior centers, assisted living facilities, or group exercise classes that already promote fall-prevention activities. However, before we can widely apply these interventions for general health and fall prevention purposes, we must understand their mechanisms and have evidence to guide their implementation. For example, there is little to no guidance on how to safely transition from traditionally cushioned shoes to minimal footwear (Futrell et al., 2024). Going from cushioned supportive shoes that essentially brace the foot, to a shoe that promotes foot mobility, places new demands on musculoskeletal structures. Just as with any activity that places new demands on muscles and joints, gradual and progressive load is necessary to prevent injury. The same can be said for specific IFM strengthening exercises. Improper technique could lead to joint alignment faults or muscle substitutions. Therefore, evidence is necessary to guide providers on how to best implement these promising interventions for their older adult patients and clients. When performed correctly, these are simple, safe, and affordable interventions that could have a major influence on older adults’ fall risk, mobility, and independence.

The use of ultrasound imaging in physical therapy research and practice has only recently become common. Clinical testing of IFM strength is difficult to isolate from the extrinsic foot muscles. Those methods are in development, but have not been established (Bruening et al., 2019; Ridge et al., 2017). Ultrasound imaging is the only method with which to directly measure changes in IFM size, and therefore, can be used as an indirect measure for increased strength. An increase in muscle size (hypertrophy) implies an increase in muscle strength. Ultrasound imaging of the IFM has been performed in research regarding young and middle-aged adults, and has also been performed successfully in at least one observational study involving older adults (Mickle et al., 2016a).

Aside from the measurement approach, the topic of IFM research in general is innovative as it has only recently begun building a body of evidence. This is especially true for an older adult population. Much of the information regarding the *function* of the IFM is speculative and has not been formally studied. We know very little about these muscles in younger or older adults, but the research that exists shares the common theme that these muscles are important because they are the first point of contact between our bodies and the environments we navigate.

### Potential limitations and solutions

We acknowledge a few limitations of this study, with possible solutions or mitigations.

Falls are multifactorial and caused by internal and external factors. The specific inclusion and exclusion criteria of this study attempts to minimize many internal confounding factors including poor foot sensation, vestibular disorders, cognitive impairments, amputations, and recent injury or surgery.

The participants will be asked to self-report falls, details of falls, intervention adherence, and step count in a paper journal. We recognize that self-reported data can be inaccurate or unreliable; however, we have mitigated this with a plan to contact participants every 2 weeks as a reminder and a supplemental way to collect this same data.

Our decision to collect foot measures using only the right foot is one based on time and resources for both researchers and participants. We recognize people can have asymmetry in the feet in terms of foot dominance, structure or pathology. Having only right foot measures limits the generalizability of our results.

The study will be conducted in an area of the United States with extremely cold winter weather. This may limit some participants’ ability to engage in the prescribed walking/wearing schedule of the minimal footwear. We will recommend people walk in minimal footwear in safe indoor spaces such as grocery stores or shopping malls, but accessibility to those spaces may be limited based on socioeconomic status. In addition, it is possible that participants wearing minimal footwear will be more unstable initially compared to their customary footwear. The walking/wearing schedule takes this into account with a very conservative increase in wear time to allow for the musculoskeletal and neuromuscular systems to gradually adapt to the footwear’s wider, thinner design.

This study addresses the very substantial clinical and community health issue of falls in older adults. The overall design and attention to detail will produce high quality research that may provide researchers, clinicians, policymakers, and older adults themselves with simple solutions to this highly relevant problem.

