In addition to the above interventions, all participants will be given a pedometer (3D Fit Bud, 3D Active, United Kingdom) and asked to record daily step count in a paper journal. This will allow for comparisons of general physical activity level of each group. Also in the paper journal, participants will be asked to record any falls and the details of the circumstances should a fall occur. To promote intervention adherence and to capture details of falls while fairly recent, participants will be contacted every 2 weeks by researchers from 4 weeks post-intervention instruction to the end of the 12-month participation period. Participants may choose their communication preference for these contacts (email, phone call, or text message). With each contact, five standardized questions will be asked, and a reminder given to not participate in other fall prevention programs while enrolled in the current study:1. Have you experienced any falls (if yes, how many and can you provide details?)2. Are you performing the study activities and do you have any questions or issues?3. Are you using your journal?4. Are you using the pedometer and recording daily step count?5. Have you had any changes in health status?

All participants will be instructed in their intervention activities, pedometer use, and journal use by six trained Doctor of Physical Therapy (DPT) students. Two students will specialize in each group’s activities. Training for each group’s activities will include individual instruction and practice with the primary investigator, who is a physical therapist with 17 years of clinical experience. After instruction, practice, and individual feedback from the primary investigator, each DPT student will individually instruct a physical therapy faculty member unaffiliated with the study, and receive feedback. Written training materials for the DPT students are the same as the instructions that will be given to research participants and can be found in Supplementary Material.

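### The two-weekly contacts are said to back up all the journal data, but the printed script duplicates only falls: it gives an unquantified adherence status and asks for no step counts

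*Protocol article*

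**What the plan says.** The section on potential limitations and solutions names the journal data: "The participants will be asked to self-report falls, details of falls, intervention adherence, and step count in a paper journal". It accepts that such data may be inaccurate and says this has been mitigated by the plan to "contact participants every 2 weeks as a reminder and a supplemental way to collect this same data". As written, the claim covers all four items.

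The Intervention section describes the contacts. They run every two weeks from week 4 after instruction to the end of the 12 months, and "With each contact, five standardized questions will be asked". The script is printed:

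- Question 1: "Have you experienced any falls (if yes, how many and can you provide details".
- Question 2: "Are you performing the study activities and do you have any questions or issues".
- Question 3 asks whether the journal is in use.
- Question 4: "Are you using the pedometer and recording daily step count".
- Question 5 asks about changes in health.

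The Statistical analysis section relies on the journal for the implementation part of this hybrid design: "Implementation variables will be analyzed quantitatively via adherence records and Likert scales". The Intervention section gives the step counts a purpose too, namely comparing physical activity between the groups.

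**The concern.** The plan recognises a weakness in its data and declares it dealt with by a specific instrument. That instrument is printed, and it does not collect what the declaration says.

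The prescription is set in days per week: 5 for 16 weeks, then at least 2 until month 12. Whether a participant met it is a count of days. If the journal is blank, lost or illegible, that count is gone, and the contacts as scripted cannot restore it. The same applies to daily steps.

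Adherence is a stated quantitative variable in a trial designed to study implementation alongside effect. The Anticipated results section also expects obstacles that differ by arm: cold weather for the footwear, toe stiffness for the exercises. A reader of the results will want to know how much of each intervention was done, and will have been told that the journals had a second source.

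**Working it through.** No figure in the plan has to be reproduced. The check sets the claimed backup beside the script, then counts what is at stake.

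**Step 1: claim against script**

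| Journal item said to be supplemented | Scripted question | What the answer yields |
|---|---|---|
| Falls | 1 | A number: duplicated |
| Fall details | 1 | Details: duplicated |
| Intervention adherence | 2 | Whether activities are being performed; no days or minutes |
| Step count | 4 | Whether steps are being recorded; no values |

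Two other statements agree with this reading. The Intervention section gives the contacts two aims, encouraging adherence and catching fall details early; collecting adherence or step data is not among them. The outcome description for fall rate, at the end of the foot-structure section, says journal entries will be checked against the contacts, and says so for falls only.

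**Step 2: number of contacts**

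Taking 12 months as 52 weeks: (52 − 4) / 2 + 1 = 25 contacts. Of these, 7 fall in weeks 4 to 16 and 18 in weeks 18 to 52.

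**Step 3: amounts the journal alone holds**

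- Weeks 1 to 16: 5 days × 16 weeks = 80 prescribed sessions, against 7 unquantified answers to question 2.
- Weeks 17 to 52: at least 2 days × 36 weeks = 72 sessions, against 18 such answers.
- Steps: about 365 daily values per participant, none requested at any of the 25 contacts.

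**Step 4: what a yes to question 2 can mean**

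If the answer is recorded as a plain yes (an assumption; the article does not say how answers are recorded), then up to week 16 it fits anything from 1 of 5 days (20%) to 5 of 5 (100%). After week 16 it does not show whether the minimum of 2 days was reached.

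**Step 5: what a 14-day count would cover**

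25 contacts × 14 days = 350 of 52 × 7 = 364 days; only the first two weeks stay uncovered. The week-16 contact looks back over weeks 15 and 16, and the week-18 contact over weeks 17 and 18. No window straddles the change in prescribed frequency. The prescribed count per window is 5 × 2 = 10 days up to week 16 and at least 2 × 2 = 4 days afterwards.

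**The case against.** The best reply is that adherence is not left without a second source. Question 2 asks about performance at every contact. Instructors meet participants at weeks 1 and 4 to go over how the intervention is being done. The 16-week interview is held with each participant and covers adherence, pedometer use and journal use, with follow-up on barriers where adherence is poor. Questions 3 and 4 also act as the reminder that the limitations section mentions, and may reduce the number of blank journals. Finally, an article may print only the question stems and leave probing and recording to a fuller form.

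Most of this stands, and it rules out several stronger readings that a reader might infer:

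- *The contacts collect nothing on adherence, or adherence has no backup.* Not supported. Question 2, the early reviews and the interview give a coarse picture.
- *A null result could not be told apart from non-performance.* Not supported in general. Returned journals and the coarse sources remain; the gap concerns participants without a usable journal.
- *The main result is compromised.* Not supported. The primary measure is the Mini-BESTest, the primary approach is intention to treat, and neither uses the journals. The per-protocol sentence sets no days-per-week threshold.
- *Adherence will be overstated because good record-keepers are also good adherers.* Plausible, but the documents do not establish it. The overstatement would equal the share of journals missing times the adherence gap between participants with and without journals. The article gives neither factor, so any number would be a guess.

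The reply does not remove the mismatch itself. None of these other sources is described as yielding a count of days or step values. The point about condensed articles has little force here, because the script is printed and called standardized, and the limitations section makes a positive claim about it.

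**Conclusion.** The point holds in a limited form. The limitations section overstates what the contacts do: the backup is real for falls and their details, partial for adherence and absent for step counts. For a participant with a missing or unusable journal, days performed against the prescription cannot be reconstructed, and the step record is lost.

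The consequence falls on the quantitative adherence analysis and the between-group comparison of activity. The number of participants affected, and the direction and size of any bias, cannot be obtained from the article. The conclusion rests on the five questions being asked as printed. If a fuller contact form already records days and steps, the printed script and the limitations section still need to be brought into line.

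**What to change.** **Main change.** Within the contacts already scheduled, reword question 2 to ask on how many of the last 14 days the study activity was done, recorded as a number from 0 to 14, and keep the open part on questions and issues. Use this count where journal data are missing, and report adherence from both sources.

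**Optional.** Have question 4 ask for the most recently recorded step counts. This protects against a completed journal that is later lost; it does nothing for one that was never filled in.

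**If the script stays as it is.** Correct the limitations section to say that the contacts back up falls, give a coarse adherence status and do not collect step counts. This is also the only remedy for contacts that have already taken place.

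**Cost.** One or two reworded questions, slightly longer contacts and a minor notification to the review board, with no added visits or staff. Recall over 14 days is approximate, so the count supplements the journal and does not replace it.
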